**Figure 2. SCORE2-Diabetes. Cardiovascular risk categories in type 2 diabetes**

*Burrowed from* 2023 ESC Guidelines for the management of cardiovascular disease in patients with diabetes (32).  *Abbreviations: CV= Cardiovascular, T2D= Type 2 diabetes, ASCVD= Atherosclerotic cardiovascular disease, TOD= Target organ damage, CVD= Cardiovascular disease.*

## Treatment algorithm:

**Figure 3. Overview of the treatment algorithm in the CMC**

**
[figure not shown]
**

- Dyslipidemia:
  Dyslipidemia is assessed by LDL status in blood samples. Patients are classified according to table 1 (32). Patients with moderate CV risk; will be recommended a LDL <2.6 mmol/L.
  Patients with high CV risk; will be recommended a LDL <1.8 mmol/L.
  Patients with very high CV risk; will be recommended a LDL <1.4 mmol/L (32).

If LDL exceed these thresholds, the treatment algorithm will be according to the following order: 1) High dose Atorvastatin, 2) Ezetimibe, 3) Referral to lipid-clinic.

- Hypertension:
  Blood pressure is measured in the examination, patients with a blood pressure >130/80 mmHg are instructed in measurement of blood pressure at home 3 times a day for three days (32). If the mean home blood pressure is >130/80 mmHg, treatment algorithm will be according to the following order:

1) ACE-inhibitor or angiotensin II receptor blocker (ARB), 2) thiazide, 3) calcium antagonist, 4) mineralocorticoid (MRA), and 5) beta blocker. If aforementioned is already supplied 6) Referral to hypertension-clinic.

In patients with a high biological age blood pressure <140/85 mmHg is accepted. Blood pressure >140/85 mmHg the above-mentioned treatment algorithm will be followed (32).

- Thrombosis prophylaxis:
  Patients with ischemic heart disease are recommended lifelong acetylsalicylic acid.
  If patients have had a new acute myocardium infarction, they will be prescribed 12 months of ADP-receptor blocker (32).

Patients with cerebrovascular disease are recommended lifelong clopidogrel treatment(32) . Patients with periphery arterial disease are recommended lifelong ASA treatment (32).

Patients with atrial fibrillation/flutter are recommended lifelong direct oral anti-coagulant (DOAC) treatment (32).

When two antithrombotic drugs are used, proton pump inhibitors are recommended to prevent gastrointestinal bleeding(32).

- Diabetes: Hyperglycemia is assessed by measurement of HbA1c. If HbA1c > 53 mmol/mol addition of antidiabetic treatment is required (32). Exceptionally, in patients with a long diabetes duration (>10 years), high age (> 65 years), and episodes with hypoglycemia, a HbA1c <58 mmol/mol will be accepted (33, 34). The standard treatment algorithm will be according to the following order: 1) Biguanides 2) SGLT2 inhibitor, 3) GLP-1 receptor agonists 4) Insulin. In patients with atherosclerotic cardiovascular (ASCVD) treatment with a SGLT2 inhibitor and/or GLP-1 receptor agonist will be first. If insulin treatment is required, an endocrinologist will be contacted.
- Microvascular complications: - Nephropathy: Defined by reduced eGFR <60 ml/min and/or increased urine albumin/creatinine ratio (UACR) >30mg/g. Patients will be treated with maximum tolerable dosis of 1) ACE-inhibitor/ARB and SGLT2 inhibitor. 2) Finerenone, if 1) is fulfilled and either: eGFR>60 ml/min + UACR 300 mg/g or eGFR< 60 ml/min + UACR >30 mg/g (32).
  If further assessment of nephropathy is required, a nephrologist will be contacted.

- Retinopathy: Compliance with ophthalmologist check-ups. If non-obedient referral to ophthalmologist check-up.

- Evaluation of liver fibrosis: Systematic screening using serological test with FIB-4 will be performed at baseline and at the 3 years follow-up visit. Patients with moderate risk (FIB-4: 1.3 - 2.67) at baseline and at 3 years follow-up and patients with high risk (FIB-4: > 2,67) will be referred to the department of gastroenterology for a Fibro-scan. In case of suspicion of fibrosis or cirrhosis an individual risk assessment will be made by a hepatologist.

- Evaluation of prescription of SGLT2 inhibitor and/or GLP-1 receptor agonist:
  SGLT2 inhibitor will be prescribed if one of the following are present (32) :

1. Heart failure (regardless of ejection fraction)

2. Chronic kidney disease

3. Atherosclerotic heart disease

4. In patients with a high or very high CV risk (table 1).

GLP-1 receptor agonists will be prescribed if one of the following are present (32):

1. If further hyperglycemic control is needed on top of treatment with Biguanid and/or SGLT2-i.
2. In patients with a very high CV risk (table 1).

3. Preferences towards further weight loss (BMI>35).

- Lifestyle:
  Medical history regarding lifestyle and behavior is obtained, and recommendations for lifestyle changes will be provided (32). Alcohol consumption is recommended to a max of 10 units weekly (35), and if diagnosed with atrial fibrillation/flutter max of 8 units weekly (36). If patients are actively smoking, smoking cessation is recommended. Patients are motivated, and if interested referred to cessation courses (32). A Mediterranean diet supplemented with olive oil and/or nuts reduces the incidence of major CV events in patients with CVD (32). Patients are recommended physical activity of at least 30 minutes daily. If interested, patients can be referred to training sessions. Patients with a BMI >30 is recommended for weight loss and can be referred to a dietician or treatment with GLP-1 analogs may be considered (32).

### Peripheral artery disease/foot ulcer:

1) Patients with critical ischemia (including: resting pain, ischemic ulcers, or gangrenous ulcers) will be referred to the outpatient clinic of vascular surgery (32, 37).

2) Patients with or without symptoms of intermittent claudicatio and ABI>1,4 will be referred to examination with toe-brachial index (TBI) at the department of Endocrinology. If TBI is abnormal, patients will be diagnosed with lower extremity artery disease (LEAD), and treatment with ASA and high dose statins therapy will be initiated. Target LDL level <1.4 mmol/L (32, 37).

3) Patients with or without symptoms of intermittent claudicatio and ABI<0.9 are diagnosed with lower extremity artery disease (LEAD), and treatment with ASA and high dose statins therapy will be initiated. Target LDL level <1.4 mmol/L (32, 37).

4) Patients with diabetic foot ulcers will be referred to the outpatient clinic for wounds (32, 37).

5) Patients with abnormal monofilament test and symptoms of neuropathy will be referred to the department of endocrinology (32).

- Vaccinations:
  Anamnesis regarding vaccination status is obtained, and recommendations of yearly influenza vaccination (38). COVID vaccinations (39) after current local guidelines.

Examinations
1) Blood samples will be drawn at the baseline visit and at the three years follow-up visit. Approximately 80 ml of blood will be collected. Blood samples will be analyzed for; Hematology: Hemoglobin and leucocytes.
Lipid profiles: Total cholesterol, high-density lipoprotein (HDL), low-density lipoprotein (LDL), and triglycerides. Diabetes status: Glycated haemoglobin (HbA1c). Liver function: Alanine transaminase (ALAT), alkaline phosphatase, and gamma-glutamyl transferase (GGT), lactate dehydrogenase (LDH), and FIB-4 index for liver fibrosis assessment. Cardiac markers: N-terminal-pro b-type natriuretic peptide (NT-proBNP) and troponin T. Electrolytes: Sodium and potassium. Renal function: Creatinine and estimated glomerular filtration rate. Inflammatory marker: C-reactive protein (CRP).

2) Urine samples will be collected at the baseline visit and at the 3 year follow-up visit and albuminuria will be evaluated. This will include measurement of urine albumin and creatinine to calculate the albumin creatinine ratio (UACR) from a spot urine sample.

3) Blood pressure measurement: Blood pressure will be measured at baseline and at the 3 year follow-up visit. If blood pressure is above 130/80 mmHg after 10 minutes the CMC group will measure blood pressure at home (3 times daily for 3 days) and be treated according to the Cardio-metabolic treatment algorithm. Patients in the control group will be advised to contact the general practitioner (GP) in case of blood pressure above 130/80 mmHg.

4) Ankle-brachial index (ABI): ABI will be assessed at the baseline visit and at the 3 year follow-up visit. During the procedure, patients will be instructed to lie down in a supine position and rest for a period of 10 minutes. Blood pressure measurements will be performed in both the brachial arteries and the dorsalis pedis arteries using a blood pressure cuff and a Doppler ultrasound devise. ABI will hereby be calculated.

5) Monofilament test: will be performed at the baseline visit and at the 3 year follow-up visit. This test involves applying a 10-g monofilament at the distal plantar aspect of both great toes and metatarsal joints to assess pressure sensation.

5) Transient Elastography (Fibro-scan): Patients will be evaluated for liver fibrosis using serological test with FIB-4 at baseline and at 3 year follow-up visit. Patients with high risk (FIB-4: > 2,67) or moderate risk (FIB-4: 1.3 - 2.67) at baseline and at 3 year follow-up will be referred to the department of gastroenterology for a fibro-scan. In case of suspicion of fibrosis or cirrhosis an individual risk assessment will be made by a hepatologist.

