**Figure 1: Screening and management program in the Cardio-Metabolic Clinic**

[figure not shown]

*Abbreviations: T2D= Type 2 diabetes, CVD= Cardiovascular disease, GP= General practice, CMC= Cardio-Metabolic clinic, CG=Control group, CV= Cardiovascular, ACS= Acute coronary syndrome, HF= Heart failure.*

Baseline visit
All participant data, including detailed medical histories, will be digitally captured in the electronic-Case Report Form (REDCap). The assessments will encompass: Duration and diabetes-related complications, demographic data (gender, age), cardiovascular disease (including heart failure, ischemic heart disease, atrial fibrillation, valve diseases, peripheral arterial disease, stroke), risk factor status (including hypertension, hypercholesterolemia, smoking habits, alcohol consumption, familiar disposition to ischemic disease), and a detailed record of pharmacological treatments including vaccinations.

Verification of diabetes-related complication such as retinopathy, nephropathy, and neuropathy will be conducted via the Danish Adult Diabetes Database.
Physical examination will be executed, including anthropometric measurements (height, weight, and hip/waist ratio), and blood pressure will be measured after a 10-15 minutes rest period. Additionally, evaluations will include an inspection for diabetic foot ulcers and measurement of the ankle/brachial index (ABI). Electrocardiographic monitoring will be performed.

Biochemistry: Blood and urine samples will be collected. Albuminuria will be evaluated from a spot urine sample. Patients with high levels of the biomarker FIB 4 will have a Fibro-scan performed.

Randomization
Participants, which fulfill the inclusion and exclusion criteria, will be randomized to one of the following programs in a ratio of 2:1. Randomization will be performed using the randomization module available in the REDCap system.

1. Cardio-metabolic group (CMC): Specialized multidisciplinary management of T2D in a Cardio-Metabolic Clinic with a focus on the management of cardiovascular risk factors and assessment of all micro- and macrovascular complications.

2. Control group (CG): Standard of care management of T2D. This consists of a collaboration between the general practitioner and/or endocrinology outpatient clinic and/or cardiology outpatient clinic.

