**Three-year follow-up visit:**
At the three-year follow-up, all participants will undergo the same evaluation program as outlined during the baseline visit. They will be evaluated for clinical events related to the primary and secondary outcomes. Blood- and urine samples will be collected from all participants.

Efforts will be made to ensure that participants attend and complete the three years follow up visit. Participants will receive their appointment for this visit during the baseline visit. Additionally, they will be sent an electronic letter one month before the scheduled follow-up and will be reminded by a telephone call from the study staff.

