| To compare the occurrence of microvascular complication, nephropathy, in patients receiving optimal diabetes care in a Cardio-Metabolic Clinic versus usual care | - Change in urinary albumin-to-creatinine ratio (UACR) |
| Units of measure: Measured in ratio to baseline. | Time Frame: From baseline to 3 years of FU. |
| To compare the occurrence of microvascular complication, nephropathy, in patients receiving optimal diabetes care in a Cardio-Metabolic Clinic versus usual care | - Change in Chronic Kidney Disease (CKD) stage   Calculated by eGFR and albuminuria. |
| Units of measure: Measured in ratio to baseline. | Time Frame: From baseline to 3 years of FU. |
| To compare the occurrence of microvascular complication, nephropathy, in patients receiving optimal diabetes care in a Cardio-Metabolic Clinic versus usual care | Time to first occurrence of a composite CKD endpoint consisting of:   - a decline in eGFR of more than 50%, - onset of end-stage kidney disease (dialysis, eGFR<15, kidney transplantation) - death from renal or CV causes |
| Units of measure: Measured in count of events. | Time Frame: From baseline to 3 years of FU. |
| To compare the occurrence of microvascular complication, liver fibrosis, in patients receiving optimal diabetes care in a Cardio-Metabolic Clinic versus usual care | - Change in fibrosis-4 (FIB-4).   FIB-4 is calculated using age, aspartate aminotransferase (ASAT), alanine aminotransferase (ALAT), and platelet count. |
| Units of measure: Measured in ratio to baseline. | Time Frame: From baseline to 3 years of FU. |
| To compare the occurrence of microvascular complication, liver fibrosis, in in high-risk patients receiving optimal diabetes care in a Cardio-Metabolic Clinic versus usual care | - Change in degree of liver fibrosis through a Fibro-scan |
| Units of measure: Measured in count of events. | Time Frame: From baseline to 3 years of FU. |

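### The Fibro-scan trigger is worded three ways; read together, the wordings leave change in fibrosis measurable only in participants selected by year-3 FIB-4, a post-randomisation value

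*Protocol*

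**What the plan says.** The outcomes table lists "Change in degree of liver fibrosis through a Fibro-scan", from baseline to 3 years, for "liver fibrosis, in in high-risk patients receiving optimal diabetes care in a Cardio-Metabolic Clinic versus usual care". It does not say at which visit high risk is determined.

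Three places say who is scanned:

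- Baseline visit, biochemistry: "Patients with high levels of the biomarker FIB 4 will have a Fibro-scan performed". No cut-off is given.
- Treatment algorithm, evaluation of liver fibrosis: "Patients with moderate risk (FIB-4: 1.3 - 2.67) at baseline and at 3 years follow-up and patients with high risk (FIB-4: > 2,67"), are referred. The two-visit condition is attached to moderate risk. The high-risk clause names no visit.
- Examinations, transient elastography: "Patients with high risk (FIB-4: > 2,67) or moderate risk (FIB-4: 1.3 - 2.67) at baseline and at 3 year follow-up will be referred". Here the two visits follow both risk levels.

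For year 3, the follow-up section says that "all participants will undergo the same evaluation program as outlined during the baseline visit", which repeats a scan that depends on FIB-4. FIB-4 itself is planned for all participants at both visits, and its change is a separate secondary outcome not limited to high-risk patients. The Statistics section promises intention to treat, and testing in hierarchical order following the list of objectives.

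**The concern.** A change needs two scans. If the second is done only when FIB-4 is still raised at year 3, the participants with a measured change are chosen by something that happens after randomisation and that the intervention may alter, since the clinic works on weight, glucose and lipids. The arms would then be compared in differently selected groups, and participants whose FIB-4 fell most would be the ones without a second scan. The Discontinuation section deals with people who miss the year-3 visit. It does not cover people who attend but are not rescanned. A later analysis plan can choose how to handle missing scans, but it cannot supply scans that the referral rule never called for.

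**Working it through.** **Step 1: who gets two scans.** Reading A fits the three statements together: a scan if FIB-4 is high at a visit, or moderate at both visits. Reading B takes the Examinations sentence alone: a scan at each visit where FIB-4 is high or moderate.

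| FIB-4, baseline to year 3 | A: baseline / year 3 | B: baseline / year 3 |
|---|---|---|
| High to high | yes / yes | yes / yes |
| High to moderate | yes / no | yes / yes |
| High to below 1.3 | yes / no | yes / no |
| Moderate to moderate | no / yes | yes / yes |
| Moderate to high | no / yes | yes / yes |

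Under A only the first row has a change. Under B a baseline-high participant loses the second scan only by falling below 1.3. B does not sit easily with the Baseline visit section, which mentions only high levels.

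**Step 2: size.** The protocol gives no figure to reproduce, and every input here is an assumption. Log FIB-4 at baseline is normal with mean ln 1.5 and SD 0.5. The share above 2.67 is then 1 − Φ(ln(2.67/1.5)/0.5) = 1 − Φ(1.153) = 12.4%. Changes in log FIB-4 and in log stiffness each have SD 0.25 and correlation 0.5 to 0.7. The clinic shifts both by −δ, with δ = 0.10 or 0.20 (roughly a 10 to 20% reduction). A baseline-high participant is rescanned if year-3 FIB-4 exceeds k. The result is the between-arm difference in stiffness change among those rescanned, by simulation.

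| k | δ | Rescanned, control | Rescanned, CMC | Observed effect | Dilution |
|---|---|---|---|---|---|
| 2.67 (A) | 0.10 | 77% | 66% | −0.084 to −0.077 | 16 to 23% |
| 2.67 (A) | 0.20 | 77% | 54% | −0.168 to −0.155 | 16 to 22.5% |
| 1.3 (B) | 0.10 | 99.96% | 99.85% | −0.0995 | 0.5% |
| 1.3 (B) | 0.20 | 99.96% | 99.5% | −0.198 | 1% |

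Dilution is 1 − observed/true, for example 1 − 0.084/0.10 = 16%. With no effect on either measure, the rescan shares are equal and the difference is zero.

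**Step 3: other inputs.** With median FIB-4 1.3, SD 0.45, SD of change 0.30, correlation 0.3 or 0.6 and effects of 0.3 or 0.5 SD, dilution is 12 to 26% at a 2.67 trigger. If the population is everyone above 1.3 at baseline and the trigger is 1.3, it is 8 to 17%.

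**Step 4: numbers involved.** If 12.4% of 1500 qualify, that is 186 participants, or 124 and 62 under 2:1 allocation. Under A, about 67 to 82 CMC participants (54 to 66% of 124) and 48 controls (77% of 62) would have two scans.

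**The case against.** The strongest reply is that the Examinations sentence, taken at face value, still refers a participant who goes from high to moderate, because that person is high or moderate at both visits. The selection then nearly vanishes in the high-risk group. This stands, and it is why the size is given for both readings. It does not settle the matter, because the other two statements support a narrower trigger.

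Second, if high risk means above 2.67 at baseline, the moderate-risk participants without a baseline scan fall outside this outcome. That is also fair, but the table does not name the visit. Someone who becomes high at year 3 would have no baseline scan under reading A.

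Third, a reader might infer that the protocol has decided to analyse only rescanned participants, and that a loss of about a fifth of the effect is established. The document supports neither. No analysis set is named for this outcome, the selection is inferred from the referral wording, and the size rests wholly on assumed inputs.

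A reader might also infer that FIB-4 cannot be calculated. The outcomes table says that "FIB-4 is calculated using age, aspartate aminotransferase (ASAT), alanine aminotransferase (ALAT), and platelet count", while the blood list gives "Hematology: Hemoglobin and leucocytes" and omits ASAT and platelets. But the same list names the FIB-4 index as an analysis, so the omission is editorial. So is the unit line: a count of events does not fit a change in degree as worded, but could mean the number of participants whose degree changed.

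**Conclusion.** The point holds as an inconsistency with consequences. Three statements of the scan trigger do not agree, and the outcome's population is not tied to a visit. On the reading that fits all three together, the outcome exists only in a subgroup defined by a post-randomisation value, which conflicts with the promised intention-to-treat analysis. Under that reading and the main assumed inputs, a real effect is diluted by 16 to 23%. Under the wider reading it is about 1% or less. With no treatment effect on FIB-4 or stiffness there is no bias, so the selection weakens a real benefit and does not create a false one. Neither size nor direction can be derived from the protocol itself. The reach is limited to one secondary outcome in a subgroup, but the outcome is in the tested list and can still be put right by wording.

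**What to change.** 1. Reconcile the trigger in Baseline visit, Treatment algorithm and Examinations, so that one rule says which FIB-4 values at which visit lead to a scan. State that it applies in both arms, because the treatment algorithm is activated only in the CMC arm. Which rule is right is for the trial team.
2. In the outcomes table, define the population of the Fibro-scan outcome by baseline FIB-4 only.
3. Use change in FIB-4, already planned in all participants at both visits, as the liver outcome in the hierarchical between-arm tests.
4. Report change on Fibro-scan descriptively, with the number rescanned by arm, unless the reconciled rule already rescans everyone who qualified at baseline.
5. Do not count unscanned participants as having no progression. Ascertainment would then depend on treatment. With a 2.67 trigger, no effect on stiffness and assumed progression cut-offs of 0.1 or 0.25 log units, that coding gave false risk ratios of about 0.91 to 0.96 for a 0.10 fall in log FIB-4, and about 0.79 to 0.89 for a 0.20 fall.
6. Editorially, add ASAT and platelets to the blood list and correct the unit line.

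The cost is that Fibro-scan change loses its confirmatory status. No extra scans or visits are needed for steps 2 to 6. Whether step 1 adds scans depends on the rule chosen.

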## Follow-up visits

**Individual visits:**If a new treatment is prescribed that causes need for further monitoring or evaluation, individual visits as either telephone consultations or attendances will be arranged. In some cases, additional blood samples, urine samples will be collected and evaluated. Efforts will be made to keep participants on study intervention until they are completed in the CMC intervention.

**Three-year follow-up visit:**
At the three-year follow-up, all participants will undergo the same evaluation program as outlined during the baseline visit. They will be evaluated for clinical events related to the primary and secondary outcomes. Blood- and urine samples will be collected from all participants.

Efforts will be made to ensure that participants attend and complete the three years follow up visit. Participants will receive their appointment for this visit during the baseline visit. Additionally, they will be sent an electronic letter one month before the scheduled follow-up and will be reminded by a telephone call from the study staff.

